Patients post stroke are usually treated intensively in the acute and subacute phases to enhance motor performance. This is because the recovery of walking and further sensorimotor and cognitive functions mainly takes place within the first 11 weeks after a stroke. A principle here is: the milder the paralysis, the faster the recovery (Jørgensen et al., 1995). As for patients with more severe disability, *the* principle of neurorehabilitation is 'use it or lose it' [function] (Shors et al., 2012). In patients with amyotrophic lateral sclerosis (ALS), training is more intensive in the first, so called active phase after diagnosis, when the physical condition is better, in order to maintain the walking and other motor functions for as long as possible (Calabrò et al., 2019). In patients with a progressive disease such as MS, Parkinson's, ALS or hereditary ataxias, a main reason for undergoing neurorehabilitation is to preserve their ability to walk (Cheng et al., 2012; Wirz et al., 2001). Neurological deficits, such as walking impairment, poor coordination and balance loss, can be reduced by intensive and repetitive task-oriented training (Nilsson et al., 2001; Van Peppen et al., 2004).

Motor learning is present in patients with mild to severe disability, based on the process of neural plasticity, and can be boosted by a range of neurorehabilitation strategies (Maier et al., 2019). The principles underlying effective neurorehabilitation are well-known yet, and these are applied in inpatient and outpatient neurorehabilitation on a routine basis. A relevant review has identified the most salient principles of motor learning based on the evidence so far. These comprise massed practice, dosage, task-specific practice, goal-oriented practice, variable practice, increasing difficulty, explicit feedback in terms of knowledge of results and implicit feedback in terms of knowledge of performance (Maier et al., 2019).

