### 5.3 Sample size

This clinical investigation will be a prospective comparative multiple case study. A comparative multiple case study design with mainly quantitative data but also qualitative data analyses and a cross-case analysis will be used. Mixing methods is a form of triangulation in research seen as mitigating the weaknesses found in single methods (Heale & Forbes, 2013). Triangulation in research is the use of more than one approach to researching a question. The objective is to increase confidence in the findings through the confirmation of a proposition using two or more independent measures (Noble & Heale, 2019). The combination of findings from two or more rigorous approaches provides a more comprehensive picture of the results than either approach could do alone (Noble & Heale, 2019). A multiple case-oriented research strategy will be adopted to acquire knowledge about the outcomes from RAGT within the 8 different patient (disease) groups, learn about similarities and differences between individual cases and neurological disorders within study intervention periods and emerging patterns (Ababacar et al., 2020; Nordbeck, 2013).

The primary outcome of this study will be the feasibility of the methods and of a larger randomised controlled trial. Based on the study design (Yin, 2014) and primary outcome, no formal sample size calculation has been carried out. Based on the different prevalence rates of the diseases investigated in this clinical investigation, 5 patients with severe stroke in the subacute phase will be included in this study, 5 patients with mild to moderate stroke in the chronic stage, 5 patients with MS, 5 patients with PD, 2 patients with spastic para- or tetraplegia caused by any type of spinal cord lesion, 2 patients with mild to medium grade hereditary ataxia, 2 patients with acute or chronic inflammatory demyelinating polyneuropathy (e.g., GBS, CIDP) and 2 patients with motoneuron disease (e.g., ALS), resulting in a total sample size of 28. Based on the study design, methods and objectives, no further patients will be included to account for attrition, which is expected at 10%.

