### 5.4 Inclusion criteria

Potential study participants must meet all listed inclusion criteria in order to be eligible for participating in this clinical investigation. Patients will be recruited into this study if they have been diagnosed with a first-ever ischemic or hemorrhagic stroke, clinically stable phase of multiple sclerosis (MS), Parkinson's Disease (PD), a spastic para- or tetraplegia caused by any type of spinal cord lesion, mild to medium grade hereditary ataxia, acute or chronic inflammatory demyelinating polyneuropathy (e.g., GBS, CIDP) or a motoneuron disease (e.g., ALS). All patients must be in a clinically stable phase of their disease. Diagnoses will be confirmed using current criteria such as the Guideline of the German Society of Neurology (2017) (Hennerici & Kern, 2017) for stroke, the revised McDonald criteria valid at the time of diagnosis (Polman et al., 2011; Thompson et al., 2018) with MS, the UK Brain Bank criteria (Hughes et al., 1992) with idiopathic PD, Guideline of the German Society of Neurology (DGN 2012) or current NICE Guideline (*Spinal injury: assessment and initial management. Spinal*

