## 8.2. Planned statistical analysis

IBM SPSS Software, release 27.0 (IBM Corporation, Armonk, NY, USA) and GraphPad Prism 9, San Diego, California, will be used for the data analyses. Statistical significance will be defined as a two-tailed p-value  $<0.05$ . The percentage of missing data will be recorded. Using Little's test of missing completely at random (MCAR) (Little, 1988) the data will be checked, signified by a p-value  $>0.05$ .

Descriptive statistics will be used for the baseline demographic variables, primary and secondary endpoints. Continuous data will be checked for normal distribution using the Shapiro Wilk Test, Q-Q plots and histograms. Raw count (absolute and relative frequencies, N (%)) will be presented for count data (N females and males, N falls, most affected body part, and N adverse events if any, adherence (N of training sessions), recruitment, retention and adherence rates) and nominal data (gender)). Medians (range; 25th and 75th percentiles) will be reported for ordinal data (MMSE, NIHSS, EDSS, UPDRS, H&Y, ASIA Scale, SARA, MAS, ONLS, ALSFRS-R, FAC, TCT, FES-I, EQ-5D-5L, BDI-II, FSS, GAS, Smiley Likert Scale), mean (standard deviation (SD)) will be reported for continuous data (age, years of education, disease duration, 10MWT, FGA, 6MWT, TUG, FSST and MFRT).

With respect to the primary endpoint of feasibility, the recruitment rate (%) will be estimated by dividing the number of consenting patients by the N of eligible patients, multiplied by 100. The retention rate determined by dividing the N of patients who completed the study by the N of the total sample, times 100. Adherence rates will be calculated by dividing the N of RAGT sessions (16x) performed by the patients, divided by the N of the scheduled RAGT training sessions over the 4 week study period, times 100 (Osterberg & Blaschke, 2005). The eligibility, recruitment and adherence rates will be calculated with their 95% CI according to the Wilson 'score' method cited by Newcombe (Newcombe, 1998); when the proportion is close to 0 or 1, a Poisson approximation as described by Brown and colleagues will be used (Brown et al., 2001). Furthermore, the number of (serious) adverse events and side effects will be reported.

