The first phase of the analysis will involve a descriptive analysis for all disease groups using the mean (SD) or median (range, 25th and 75th percentiles). The second phase of the analysis will include inferential statistics using a pre-post analysis of the data from the total sample (one group). For continuous data, a paired t-test will be performed and for ordinal data, a Wilcoxon Signed Rank test.

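### For outcomes measured in all eight disease groups, the single pooled pre-post test can reach p<0.05 through change in the five subacute severe stroke patients alone

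*Protocol*

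**What the plan says.** Section 8.2 (Planned statistical analysis) sets out two phases. "The first phase of the analysis will involve a descriptive analysis for all disease groups". The second phase consists of "inferential statistics using a pre-post analysis of the data from the total sample (one group". The tests are fixed: "For continuous data, a paired t-test will be performed and for ordinal data, a Wilcoxon Signed Rank test". No stratum term and no comparison between groups is named. "Statistical significance will be defined as a two-tailed p-value" below 0.05.

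The same section classes FAC, TCT, FES-I, EQ-5D-5L, BDI-II and FSS as ordinal, and 10MWT, FGA, 6MWT, TUG, FSST and MFRT as continuous.

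The limitations (Strengths and Limitations, also numbered 8.2) say that low power rules out efficacy testing by disease group but allows it overall. They also list the absence of a control group. The null hypothesis in section 2.4 speaks for people with neurological disorders as one population. Sections 2.1 and 4.1 state an aim of examining whether the training caused the outcomes.

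On the sample, section 5.3 states: "5 patients with severe stroke in the subacute phase will be included in this study", with the eight quotas "resulting in a total sample size of 28". On the expected course, section 1.1 says that "the recovery of walking and further sensorimotor and cognitive functions mainly takes place within the first 11 weeks after a stroke", and that patients with progressive disease train mainly to preserve walking. Section 1.3 names the severe subacute stroke patients as those expected to gain walking ability.

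**The concern.** A one-sample pre-post test answers whether the average change over the enrolled mix differs from zero. The mix here is set by quota (5:5:5:5:2:2:2:2), and the protocol expects different courses in its parts: recovery early after stroke, and preservation in progressive disease. One stratum that improves for reasons of its own can move the pooled result while the other seven stay where they were.

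At stake is what a pooled p<0.05 may be taken to show. Under the protocol's wording it would count as an overall efficacy result for neurological disorders in general. It would stand beside a stated causal aim and a planned randomised trial. These are secondary endpoints; the primary endpoint, feasibility, is not touched.

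**Working it through.** **Sample.** 4 x 5 + 4 x 2 = 28, which reproduces section 5.3. The subacute severe stroke stratum is 5/28 = 17.9%.

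**Which outcomes can be affected.** The stratum must be in the same test as the others.

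- FES-I, EQ-5D-5L and BDI-II have no restriction and are measured before and after in all groups.
- FAC is unrestricted in secondary objective 2 (section 2.3) but limited to ambulatory patients in Table 7 and in the synopsis endpoint list. The two must be reconciled.
- FSS is marked only post-intervention in Table 7, so no pre-post change exists as tabled.
- 10MWT, FGA, 6MWT, TUG and FSST are for ambulatory patients. Section 4.8 treats the severe subacute group as non-ambulatory for TCT and MFRT, so to that extent it does not enter these tests.
- TCT and MFRT, as described in section 4.8, are for non-ambulatory subacute stroke patients, so their sample is this stratum.

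**Limiting case: the five improve equally, 23 have zero change.**

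Wilcoxon, the planned test for the four affected outcomes. Zeros drop out, leaving five positive differences: W = 15, expectation 7.5.

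- Equal gains (all ranks 3): variance = 5 x 3²/4 = 11.25; z = 7.5/√11.25 = 2.236; p = 0.025.
- Unequal gains (no ties): variance = 5 x 6 x 11/24 = 13.75; z = 7.5/√13.75 = 2.023; p = 0.043.
- Exact: 2 x (1/2)⁵ = 0.0625, not significant. The protocol does not say whether exact or asymptotic p-values will be used.

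Paired t-test, which would apply if a score were analysed as continuous. With k of n patients changing by the same amount, t = √[k(n−1)/(n−k)], whatever that amount is.

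| n | k | t | p |
|---|---|---|---|
| 28 | 5 | √(5 x 27/23) = 2.42 | 0.022 |
| 28 | 4 | √(4 x 27/24) = 2.12 | 0.043 |
| 28 | 3 | √(3 x 27/25) = 1.80 | 0.083 |
| 25 | 5 | √(5 x 24/20) = 2.45 | 0.022 |

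The last row reflects the 10% attrition expected in section 5.3, with all five retained.

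**With variation.** The protocol gives no expected change or SD by group, so these are assumptions: SD 1 in every patient, mean change 0 in the 23, mean gain m in the five. Simulated chance of a significant result in the positive direction (20,000 runs), against a nominal 2.5%:

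| m (SD) | Wilcoxon | t-test |
|---|---|---|
| 1 | 11% | 12% |
| 2 | 21% | 26% |
| 3 | 25% | 39% |
| 5 | 26% | 59% |

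For FAC-type data (3,000 runs), each of the 23 moves up or down one category with probability 5-25% for each direction, and the five gain 1 to 2 categories. The pooled test is then significant in 20-84% of runs by normal approximation and in 14-57% by the exact test. With the five left out, the two-sided rejection rate is about 5% for continuous data and 2-5% for the FAC-type data.

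**TCT and MFRT.** With n = 5, an MFRT gain of 1, 1.5 or 2 SD is significant by t-test in 40%, 71% or 91% of runs. TCT by exact Wilcoxon cannot go below 0.0625.

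**The case against.** The strongest reply is that the reader will not be misled. Descriptive results for every disease group come first, and section 8.1 (General aspects of the analysis) puts comparison within and between groups at the centre. In the limiting case above, those tables would show that only one stratum moved. The trial hypotheses are to come from cross-case synthesis, not from a pooled p-value. The limitations already concede no control group, low power and limited generalisability. A sensitivity analysis could also sit in a statistical analysis plan that is not at hand.

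Much of this stands. A reader might infer that a pooled p<0.05 could not be told apart from natural recovery; that goes too far, because the group tables would partly reveal the pattern. A reader might also infer that severe subacute stroke breaches the rule that "All patients must be in a clinically stable phase of their disease". The documents do not support that: section 5.4 expressly admits these patients, the subacute phase is never defined in weeks, and a clinically stable phase need not mean unchanging function. Nor does section 1.1 call the early recovery spontaneous; it describes its timing alongside intensive treatment.

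Zero change in the other 23 is also a favourable assumption. Worsening in progressive disease would pull the pooled test towards the null, and the exactWilcoxon in the limiting case is not significant.

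What does not fall away is that the protocol fixes the pooled test, calls its purpose overall efficacy testing, and says nothing about what may be concluded if one stratum carries the result. It names no recovery-related limitation and expects no harm to the results from the limitations it lists.

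**Conclusion.** The point holds for FES-I, EQ-5D-5L and BDI-II, and for FAC if the conflict over its population is settled in favour of all patients. For these, change in 5 of 28 patients can produce p<0.05 with no change in the rest, though it need not. The planned test for all four is the Wilcoxon, so its figures carry most weight: 0.025 or 0.043 by normal approximation, 0.0625 exact, and about 11-25% positive results for assumed gains of 1-3 SD. The t-test figures (0.022; 12-39%) show the same mechanism on a continuous scale. All rest on assumed changes and SDs, since the protocol states none.

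The stronger inference that the main walking tests are distorted in the same way is not supported. If all five are non-ambulatory they contribute nothing to those tests, and at least four would have to be measured for this route to reach p<0.05 (n = 27, k = 4: p=0.043; n = 26, k = 3: p=0.083). For TCT and MFRT the issue is one of labelling: they are results of one stratum, in which recovery and training cannot be separated.

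**What to change.** 1. Reconcile secondary objective 2 with Table 7 and the synopsis on who contributes to FAC, and state the analysis population for each endpoint.
2. For FES-I, EQ-5D-5L, BDI-II and, if applicable, FAC (FSS only if a baseline is collected), report the pooled change with and without the subacute severe stroke stratum, next to individual pre-post values marked by disease group.
3. Do not describe a pooled change as cross-disease if it disappears without that stratum.
4. Report TCT and MFRT as results of the subacute stroke stratum, not of the total sample.
5. Describe all pre-post results as uncontrolled change and not as efficacy. Leaving out five patients removes one source of change only; there is still no control arm, and all patients receive concurrent multidisciplinary rehabilitation (section 7.4).

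The cost is one extra analysis and one figure per outcome, with no new patients or visits. At n = 23 the interval is wider, by a factor of about √(28/23) = 1.10 if the SD is the same.

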## 8.3 Planned qualitative data analysis

(Jotted) field notes from the semi-structured observation will be expanded in writing and then entered into Excel files. A Thematic Analysis (TA) (Braun & Clarke, 2006, 2021) will be performed. TA is a method for systematically identifying, organising, and offering insight into

patterns of meaning (themes) across a dataset. Through focusing on meaning across a dataset, TA allows to observe and make sense of collective or shared meanings and experiences. TA is a flexible method that allows focusing on the data in numerous different ways i.e., both on analysing meaning across the entire dataset or examine one particular aspect of a phenomenon in depth. The TA analysis will be performed in 6 phases as suggested by Braun & Clarke (Braun & Clarke, 2006, 2021).

### **Phase 1: Familiarising oneself with the data**

This phase involves immersing oneself in the data by reading and re-reading textual data. Making notes on the data as they are read is part of this phase. Reading data as data means reading the words actively, analytically and critically, and starting to think about what the data mean. The aim of this phase is to become intimately familiar with the dataset's content, and to begin to notice content that might be relevant to your research question.

### **Phase 2: Generating initial codes**

The systematic analysis of the data through coding is started in phase 2. Codes are the building blocks of analysis as they identify and provide a label for a feature of the data that is potentially relevant to the research question. Coding can be done at the semantic (descriptive) or the latent (interpretative) level of meaning. Codes are succinct and work as shorthand for relevant aspects of the data. Codes will almost always be a mix of the descriptive and interpretative. Coding will be done in large or small chunks; some chunks won't be coded at all. Coding requires another thorough read of every data item. Each data item will be coded in its entirety before coding another. Codes will be named and the text around it marked using an inclusive, thorough and systematic approach.

### **Phase 3: Searching for themes**

In this phase, themes are created from the dataset. A theme "captures something important about the data in relation to the research question, and represents some level of patterned response or meaning within the data set" (Braun & Clarke, 2006) (p. 82). This phase will involve reviewing the coded data to identify areas of similarity and overlap between codes. The basic process of generating themes and subthemes (the subcomponents of a theme) will involve collapsing or clustering codes that seem to share some unifying feature, so that they reflect and describe a coherent and meaningful pattern in the data. Certain concepts or issues may cut across themes and provide a unifying framework for telling a coherent story about what is going on in the data, overall. Another important element of this stage is starting to explore the relationship between themes, and to consider how themes will work together in telling an overall story about the data. Good themes are distinctive and, to some extent, stand-alone, but also need to work together as a whole. According to the recommendation from Clarke and Braun, a maximum of 6 to 7 themes will be generated. A

thematic map will be generated to outline the candidate themes, and all the data extracts relevant to each theme will be collated.

#### **Phase 4: Reviewing potential themes**

Phase 4 will involve a recursive process whereby the initially developed themes will be reviewed in relation to the coded data and entire dataset. The themes will be checked against the collated extracts of data (1. Is this a theme?) and explored whether the theme 'works' in relation to the data (2. Does this theme tell me something useful about the dataset, in relation with my research question?). If necessary, some codes will be discarded or relocated under another theme. Alternatively, the boundaries of a theme will be redrawn, so that it more meaningfully captures the relevant data (3. What are the boundaries of this theme?). It will further be checked whether there are sufficient meaningful data to support a theme (4.) and whether a theme contains coherent data (5.). If a theme does not work, it will be discarded altogether, split into two or more themes, or collapsed with another theme, and the process started again.

#### **Phase 5: Defining and naming themes**

In phase 5, it will be clearly stated what is unique and specific about each theme. Themes should ideally have a singular focus, scope and purpose (1); be related but don't overlap, so they aren't repetitive, although they may build on previous themes (2); and directly address the research question (3). This phase involves refining the analysis and starting the write-up. Extracts will be selected to quote and analyse, which provide the structure for the analysis. A descriptive TA will be used, where data tend to be used in illustrative ways, and conceptual/interpretative, where extracts tend to be analysed in more detail. Informative, concise, and catchy names will be used for naming the themes.

#### **Phase 6: Producing the report**

The purpose of the report is to provide a compelling 'story' about the data, based on the analysis.

### **8.1. Handling of missing data**

The percentage of missing data will be recorded. Using Little's test of missing completely at random (MCAR) (Little, 1988) the type of missing data (MCAR, missing at random (MAR), missing not at random (MNAR)) will be checked, signified by a p-value >0.05.

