#### **7.5 Participant drop-out**

Study participants are free to withdraw their consent from the clinical investigation participation at any time without having to give a reason and without any consequences for their future treatment. In addition, patients may be withdrawn from the study by the PI if their health is in jeopardy.

The following points or events will lead to the patient's exclusion from the study if they occur after their initial admission in the study (dropout in terms of the biometric analysis):

- No questionnaire scores, assessment scores or LEXO® measures of interpretable quality.
- Withdrawal of consent to study participation by the study participant during integration into the study.
- An MS relapse or other disease exacerbation for any of the included diseases during the intervention period.
- Any changes or adjustments to medication that has an influence on the participant's walking ability/performance.

If the patient's health is jeopardised after the study intervention has started as a result of an unexpected deterioration in their state of health or general condition and/or mental/physical training is absolutely contraindicated, participation in the study will be ended immediately and a general physician or specialist will be consulted.

The reason for the patient's departure from the study will be documented in the CRF. The study is to be continued with the next identification number, with no replacement of study participants allowed. All patients leaving the study prematurely will be asked to undergo a

final examination with regard to their safety and as part of post-intervention testing at the next possible opportunity. The results of these tests will be documented in the CRF.

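### Little's test with p>0.05 cannot classify missing data as MCAR, MAR or MNAR, and with about 3 of 28 patients missing a non-significant result says little about MCAR either

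*Protocol*

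**What the plan says.** The section headed Handling of missing data (the second one numbered 8.1) says that the percentage of missing data will be recorded and that, by Little's test, "the type of missing data (MCAR, missing at random (MAR), missing not at random (MNAR)) will be checked, signified by a p-value >0.05". Section 8.2, Planned statistical analysis, and the statistical row of the synopsis use the same test and cut-off but name only MCAR: "Using Little's test of missing completely at random (MCAR) (Little, 1988) the data will be checked, signified by a p-value" above 0.05. None of these places says what analysis follows from the result.

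The pre-post comparison in the total sample is by paired tests: "For continuous data, a paired t-test will be performed and for ordinal data, a Wilcoxon Signed Rank test". Section 5.3 fixes the numbers, "resulting in a total sample size of 28", and adds that "no further patients will be included to account for attrition, which is expected at 10" per cent. Section 7.5 lists events that end participation and count as drop-out for the analysis. Among them are "An MS relapse or other disease exacerbation for any of the included diseases during the intervention period" and a change of medication that affects walking. The same section has the reason for leaving documented and asks early leavers to take a final examination as part of post-intervention testing.

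**The concern.** The protocol gives the test a task it cannot do. Whether data are MAR or MNAR depends on the unobserved values, so no test on observed values can decide it. A p-value above 0.05 is a failure to reject MCAR. In a small sample that is the likely outcome under many mechanisms that are not MCAR.

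The plan's own drop-out rules make this matter. Patients who leave because of an exacerbation or a walking-relevant medication change have probably changed differently in walking and balance from those who stay, and walking and balance are what most secondary endpoints measure. Paired tests need both time points, so they describe completers. A report saying that missingness was checked and found to be completely at random would give the completers' change support that it has not earned.

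**Working it through.** **1. What one p-value can show.**
- p≤0.05 is evidence against MCAR. Both MAR and MNAR remain possible.
- p>0.05 means MCAR is not rejected. MCAR, MAR and MNAR all remain possible.

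Neither result gives the three-way classification. This step needs no assumption.

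**2. Inputs from the protocol.** The strata sum to 5+5+5+5+2+2+2+2 = 28, which reproduces the stated total. Attrition of 10% is 2.8, about 3 patients. The 85% retention target corresponds to 4.2 lost, about 4. The two-sided level is 0.05. The protocol states no operating characteristic for Little's test, so there is none to reproduce.

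**3. Power, one-variable approximation.** With one baseline variable and k patients lacking the post value, the test reduces to a 1-df comparison of drop-outs with completers at baseline. For a baseline difference of d SD the noncentrality is

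λ = k(28−k)/28 × d²

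For k=3 this is 3×25/28 × d² = 2.679 d². For k=4 it is 4×24/28 × d² = 3.429 d².

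| d (SD) | λ, k=3 | Power, k=3 | λ, k=4 | Power, k=4 |
|---|---|---|---|---|
| 0.5 | 0.670 | 13% | 0.857 | 15% |
| 0.8 | 1.714 | 26% | 2.194 | 32% |
| 1.0 | 2.679 | 37% | 3.429 | 46% |

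For 80% power, d = (1.96+0.84) × √[28/(k(28−k))], which is 1.71 SD for k=3 and 1.51 SD for k=4.

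**4. Power by mechanism (simulation, 3 of 28 missing).** Assumptions not in the protocol: normal data, pre-post correlation 0.7, one or three outcomes correlated at 0.4.

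| Drop-out depends on | Odds per SD worse | Share of runs with p>0.05 |
|---|---|---|
| Baseline (MAR) | ×2 to ×3 | 59–90% |
| Post value (MNAR) | ×2 to ×7.4 | 62–94% |
| Change not predicted by baseline (MNAR) | ×3 to ×7.4 | 94–97% |

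In the last row the test rejects in about 3% to 6% of runs, about the rate found under true MCAR (4% to 5%), however strong the mechanism.

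**5. Effect on the completers' change.** The model is 28 standard normal changes with true mean zero, 3 removed and a paired t-test on the remaining 25 (100,000 runs). The removal odds per SD of worse change are assumed. Bias is in SD of the change.

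| Removal | Bias | True null rejected |
|---|---|---|
| Unrelated to change | 0.00 | 5% |
| Odds ×1.5 | +0.05 | 6% |
| Odds ×2 | +0.07 | 7% |
| Odds ×3 | +0.11 | 10% |
| Odds ×7.4 | +0.16 | 15% |
| Exactly the 3 worst | +0.20 | 23% |

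The last row is the upper bound for three losses.

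**6. Would imputing zero change repair it?** In the upper-bound case, adding three zero changes moves the bias only from 0.198 to 0.177 SD and the rejection rate from 22.9% to 22.8%, because mean and SD shrink together. The standard Wilcoxon test discards zero differences altogether. Zero change alone is therefore not a protective assumption.

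**The case against.** The strongest defence is that nothing hangs on the test. No imputation, analysis set or estimator depends on its result. The primary endpoint is feasibility, section 5.3 says that "no formal sample size calculation has been carried out", and the protocol calls the effects preliminary and lists the missing control group as a limitation. This stands, and it limits the harm to what is reported.

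A reader might also infer that Little's test is the plan's only provision for missing data. That is not supported: reasons for non-retention and departure are recorded (sections 4.8 and 7.5), uncollected data are to be marked as such on the case report form (section 10.4), and a final examination is requested from early leavers. What is not stated is any analysis that uses those values, and 7.5 still counts these patients as drop-outs.

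It is likewise tempting to say that all pre and post variables enter one joint test, with walking tests in non-ambulatory patients counted as missing, so that the covariance matrix cannot be estimated. The protocol does not say which variables enter, and that detail may sit in an analysis plan not at hand.

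Finally, the power figures rest on a one-variable approximation and on assumed mechanisms. With 6 drop-outs, a single outcome and a strong mechanism, the share with p>0.05 falls to about 35% to 42%. At the protocol's own 10% attrition it stayed at 59% or above in every scenario tried.

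**Conclusion.** The point holds as an error in a stated method. That Little's test cannot yield the three-way classification follows from its null hypothesis alone. That p>0.05 is weak evidence here follows from about 3 losses among 28 patients: power of about 13% to 37% against baseline differences of 0.5 to 1.0 SD, and near 5% when loss depends on unpredicted change.

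The size of the bias, about +0.05 to +0.16 SD with 6% to 15% false rejection, rests on assumed drop-out odds and normal changes. A reader might take +0.20 SD and 23% as what to expect, but these require the three losses to be exactly the three worst changes. The protocol gives no drop-out mechanism, so it does not support treating that extreme as typical. In this model, loss of the worse changes always shifts the mean in favour of the intervention. The endpoints affected are secondary and no decision rule uses the test, so this should be corrected but does not threaten the primary objective.

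**What to change.** In the missing-data section, in 8.2 and in the synopsis:

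- Delete the MCAR/MAR/MNAR classification. If Little's test is kept, call it descriptive and state that p>0.05 does not show MCAR.
- Tabulate missing post-intervention values by the reasons already recorded and by stratum, with tests not applicable because of ambulatory status shown separately.
- Give the complete-pair change alongside a sensitivity analysis that includes the final-examination values obtained from early leavers under 7.5. Where none was obtained, set the missing changes over a stated range that includes worsening, not zero change alone.
- State that 7.5's wording on drop-out for the analysis does not bar these values from the sensitivity analysis.

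No new data are needed. The cost is revised wording, one more table and possibly a less favourable estimate. Early leavers are only asked to attend the final examination, so some values will still be missing.
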